## Introduction

1.

Preterm birth remains a public health emergency associated with high morbidity and mortality, leading to substantial emotional and financial burden for individuals, families, and communities (1–4). Infants born very preterm (VP, before 32 weeks gestation) often require several months of hospitalization in the neonatal intensive care unit (NICU). This is a time during which the preterm brain volume quadruples in size and is highly sensitive to both positive and negative environmental experiences (5). Yet, this is also a period that VP infants spend in the sensory-atypical environment of the NICU composed primarily of procedural touch, loud alarm noises, and bright lights (6). Alternatively, the NICU environment could consist of silence and a paucity of enriching stimuli such as human voice, touch, and interaction. Recent work suggests that adequate development of sensory functions in early infancy create the foundation for resilient higher-order cognitive, behavioral, and social-emotional processes later in life (7–9). Despite the attention that the neurosensory environment has received in the last decade, there is a paucity of safe and feasible early interventions supported by neurobiologically-based evidence to optimize the sensory environment and improve the neurodevelopmental trajectories of VP infants.

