#### Timeline of MRI scans

2.6.1.

In our NICU, the clinical standard of care entails that babies born extremely preterm (before 28 weeks gestation), or VP (28–32 weeks gestation) with additional risk factors such as moderate-severe bronchopulmonary dysplasia, stage II or higher necrotizing enterocolitis, need for major surgery, severe growth restriction, or documented neurological abnormality on CUS among others, are considered for a TEA brain MRI. The TEA scan typically occurs between 38 and 42 weeks PMA or within the week of discharge, whichever comes first. Infants typically undergo brain MRI scanning without sedation in the study unit (20), using the documented “feed and wrap” method (32) (Figure 2). Serial CUS imaging is also obtained routinely in our unit for babies born before 32 weeks gestation per a clinical practice guideline, typically on days of life 1, 3, 7, 30, and 60. However, with only scarce evidence-based understanding of the etiology of many neuronal disorders available, findings on both serial CUS and TEA MRIs leave many unanswered questions in terms of etiology, timing, and evolution of injury prior to TEA, which have implications for the child's developmental trajectory and therapy needs post NICU discharge.

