An infant will subsequently be assigned to the appropriate SENSE risk group (low-risk vs. high-risk) based on the results of the early CUS and MRI findings (if the first brain MRI is able to be completed at enrollment). If an infant is in a critical condition (i.e., receiving invasive mechanical ventilation or unstable on high level of noninvasive ventilation support) that does not permit safe scanning in the in-unit scanner, we will utilize the CUS results to determine assignment to an SENSE risk group, with plan for the first MRI imaging to be obtained as soon as the clinical status permits. If at any point an infant initially assigned to the low-risk group meets criteria for the high-risk classification based on identification of neurological injury on subsequent imaging, the infant will be transitioned to the SENSE-plus group to received enhanced neurorehabilitative support as outlined in Table 1. Enrolled VP infants in the low- or high-risk groups will be scanned at a frequency of approximately every 2 weeks, from the time of enrollment until TEA (approximately 38–42 weeks PMA) or until NICU discharge, to monitor brain growth and evolution of any injury. At TEA, infants enrolled in the low-risk or high-risk groups will undergo brain MRI in an off-unit Siemens Trio 3 Tesla scanner (Erlangen, Germany) equipped with a 16 channel pediatric head coil and 1 mm isotropic voxels. This schedule of serial imaging will inform characterization of patterns of brain growth of the VP infant throughout their NICU course, along with a broader understanding of the brain injury that occurs over the course of VP infants’ hospitalization.

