### Sample size

2.8.

For the primary aim, the proposed study has ≥80% power to detect differences in brain growth (total brain volume) on MRI at TEA between the SENSE (low- and high-risk groups combined) and reference groups of moderate to large effect sizes (Cohen's *d* = 0.70) using a two-tailed test with α=0.05. The power of the proposed study is sufficient to detect effect sizes reported in studies including a trial of early sensitivity training in parents of preterm infants (*n* = 45) which reported large effect sizes of *d* = 0.75–1.10 in white matter maturation and connectivity by ADC and FA between groups (46). The proposed study is further powered to detect small to moderate effect sizes (*d* = 0.41) between repeated brain measurements and moderate effect sizes (*d* = 0.59) in each SENSE subgroup individually (SENSE or SENSE-plus, *n* = 25 each) (Aim 2). Brain growth measured as total tissue, unmyelinated white matter, and cortical gray matter have been previously reported to exhibit moderate to very large effect sizes (*d* = 0.72–2.41) when comparing measures before and after 33–34 weeks gestational age (17).

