### Data analysis

2.10.

Descriptive statistics of key demographic and clinical characteristics will be reported overall and by group status (exposed vs. reference) using means and standard deviations (or medians and interquartile ranges, as appropriate) for continuous and number and percentage for categorical variables. Differences by group status will be tested using chi square (or Fisher's exact test where cells <5) and Wilcoxon rank sum or Kruskal-Wallis tests, as appropriate, for categorical and continuous variables, respectively. Similar statistics will be reported by risk status among exposed infants including fidelity of implementation of the SENSE or SENSE-plus program in the low-risk and high-risk groups (>75%, 50%–75%, 25%–50%, and <25% compliance with total amount of recommended sensory exposure in each category). For the primary aim, outcome among infants in the SENSE program (exposed group) will be compared with the unexposed, similarly eligible infants whose families did not enroll in the neuropromotive program. Differences in outcome by group status will be analyzed using linear mixed models [or multinominal regression using generalized estimating equations (GEE) for ordinal categories of injury] to adjust for intrafamilial correlation among multiple births in models unadjusted and adjusted for potential bias (selection and confounding) by baseline covariates associated with both SENSE status and outcome. The study will also examine the difference between groups by exposure and high/low risk status, i.e., high risk: exposed vs. unexposed and low risk: exposed vs. unexposed. To address small sample size, we will utilize robust estimation methods. We will use a similar approach to assess differences between exposure groups for Aim 3 outcomes assessed at NICU discharge and at age two corrected age. Analysis of the change in repeated measures (Aim 2, SENSE groups only) will be modeled using linear mixed models and GEE, as appropriate, with fixed effects for SENSE group status, time, and the interaction between group and time. For assessment of change between two assessment time points, models will include fixed effects for group status and baseline assessment. We will use a similar approach to model Premie-Neuro exam scores (Aim 3) assessed at each serial MRI measurement for exposed infants. Analyses are exploratory and thus multiple comparisons will not be adjusted. Statistical analyses will be run using SAS v9.4 software (SAS Institute Inc., Cary, NC, USA) and IBM SPSS version 24.0 (IBM Corp, Armonk, New York, USA).

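### The stated adjustment rule for the primary brain-volume comparison does not admit postmenstrual age at the term-equivalent scan, although volume depends strongly on that age and scans may be weeks apart

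*Protocol article*

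**What the plan says.** Section 2.8 of the protocol article powers the study for "differences in brain growth (total brain volume) on MRI at TEA between the SENSE (low- and high-risk groups combined) and reference groups", at d = 0.70, "using a two-tailed test with α=0.05", with at least 80% power. Section 2.2 gives 25 infants in each of the two exposed groups and 25 in the reference group.

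Section 2.10 compares the groups with linear mixed models, unadjusted and "adjusted for potential bias (selection and confounding) by baseline covariates associated with both SENSE status and outcome". The limitations paragraph of the Discussion says the same: baseline demographic and clinical characteristics are compared and models adjusted as appropriate. A time term appears only in the Aim 2 models, which use the SENSE groups alone.

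On scan timing, section 2.6.1 describes unit practice: "The TEA scan typically occurs between 38 and 42 weeks PMA or within the week of discharge, whichever comes first". For the exposed groups the same section plans scans "from the time of enrollment until TEA (approximately 38–42 weeks PMA) or until NICU discharge". Sections 2.2 and 2.3 say that reference infants are those who have a brain MRI around term for clinical or other research reasons. The Introduction says that during the months of hospitalization the "preterm brain volume quadruples in size".

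**The concern.** A single brain volume taken during rapid growth reflects the infant's age on the scan day as well as anything done beforehand. PMA at the scan is a property of the outcome measurement and not a baseline characteristic. A rule that admits only baseline covariates does not reach it. Even if it were counted as baseline, it would enter only if found to be associated with SENSE status.

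Two things are at stake. If mean scan age differs between the groups, part of the age difference is read as a SENSE effect, or hides one. If the mean ages are equal, the spread of ages still adds variance that the model could remove.

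The point concerns the cross-sectional TEA contrast, not the Aim 2 models of change over time.

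**Working it through.** **Inputs from the article.** 50 against 25 infants; d = 0.70; two-sided α = 0.05; power at least 80%; TEA window about 38–42 weeks, open below 38 through discharge; volume quadruples over several months.

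**Assumptions, because the article gives no SD and no weekly growth rate.** The fourfold growth takes 12–16 weeks. The between-infant SD at a fixed age is 10–12% of term volume. Scan ages are uniform over four weeks, so their SD is 4/√12 = 1.15 weeks.

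**1. The plan's own figure.** Noncentral t, 50 against 25, d = 0.70: power 80.5%. The stated power reproduces.

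**2. Growth per week, as a share of term volume.**
- Linear: 0.75/16 = 4.7% to 0.75/12 = 6.25%.
- Exponential: ln 4/16 = 8.7% to ln 4/12 = 11.6%.

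I carry forward 4.7–8.7%, that is, from the slowest linear rate to the slower exponential rate.

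**3. One week of PMA in SD units at fixed age.** b = weekly growth / SD.
- Lowest: 4.7/12 = 0.39.
- Highest linear: 6.25/10 = 0.62 (0.625).
- Exponential at 8.7%: 8.7/12 = 0.72 to 8.7/10 = 0.87.

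The mean age gap worth 0.70 SD is 0.70/b: 0.70/0.87 = 0.8 week to 0.70/0.39 = 1.8 weeks.

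**4. False positives with no SENSE effect and no age term.** The age spread inflates the observed SD by √(1 + (1.15b)²), which is 1.10 at b = 0.39 and 1.41 at b = 0.87. A mean gap of g weeks gives a standardized bias of g·b divided by that factor.

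| Gap in mean scan age | Bias, b = 0.39 | Bias, b = 0.87 | Rejection rate |
|---|---|---|---|
| 0 | 0 | 0 | 5% |
| 0.5 week | 0.18 | 0.31 | about 11–24% |
| 1 week | 0.36 | 0.61 | about 30–70% |

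These gaps are illustrations. The article reports no gap.

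**5. Power with no gap.**
- If d = 0.70 is in units of the SD at fixed age, the effective d is 0.70/1.10 = 0.64 down to 0.70/1.41 = 0.49 (unrounded factors). Power falls from 80.5% to about 73% and 51% respectively.
- If d = 0.70 is in units of the SD actually observed across TEA scans, the age spread is already in the denominator. Power stays at 80.5%, and adjusting for age would improve precision beyond that.

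Section 2.8 does not say which SD is meant.

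**The case against.** The strongest objection is that this is a condensed article. Section 2.10 gives a general rule for selection and confounding bias and lists no covariates at all, not even sex or gestational age at birth. A fuller plan, not shown, might include PMA at scan. That is possible, and it lowers the certainty that the term will be missing from the final model. It does not remove the point: the article states a selection rule, and a plan that followed it would not admit this variable.

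Three stronger readings are tempting and are not supported.
- A reader might infer that reference infants are scanned earlier than SENSE infants. Section 2.6.1 lets scanning end at discharge for SENSE infants too, so the documented windows are close to the same. The real difference is that the study does not set the timing of reference scans.
- A reader might infer that one week of age difference equals the whole target effect. At fixed age it exceeds 0.70 SD only at the exponential rate. Under linear growth it is 0.39–0.62. In observed-SD units it is 0.36–0.61 and never reaches 0.70 within the assumed range.
- A reader might infer that the stated power is wrong. It reproduces, and it is eroded only if 0.70 is scaled to the SD at fixed age.

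The article also calls its analyses exploratory and its findings preliminary. That limits what will be claimed from them, but it is no reason to leave a removable source of bias in the one group comparison for which the study is powered.

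Finally, scan age may partly follow exposure, because discharge can set the scan date. That part of the objection stands and shapes the fix.

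**Conclusion.** The point holds as a weakness in the stated adjustment rule. As worded, section 2.10 does not admit PMA at the TEA scan into the primary volume comparison, while scans in both groups can fall four weeks or more apart and the timing of reference scans lies outside the study's control. A difference in mean scan age is possible; its size and direction are not documented.

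On the assumed growth and SD, a week of age is a large part of the target effect, and a half-week gap would at least double the nominal 5% error rate. Whether power also suffers turns on a scaling that the article does not state. All the sizes rest on the assumed growth rates, SD and uniform spread of scan ages, not on figures in the article.

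**What to change.** In section 2.10, state that PMA at the TEA scan, in days, is a prespecified covariate in the adjusted primary TEA volume model, whether or not it is associated with SENSE status. Leave the crude model crude, or add a model adjusted for scan age alone. Report the distribution of scan age by group.

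Add a sensitivity analysis limited to scans at 38–42 weeks PMA in both groups. Note beside it that scan age may partly follow exposure through discharge timing, so the age-adjusted and crude estimates should be read together. It would also help to say in section 2.8 which SD the 0.70 refers to.

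The cost is one degree of freedom and a little more analysis. Scan date and gestational age are already held, so no new data are needed.

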
## Discussion

3.

To our knowledge, this is the first study to follow brain growth and injury in VP infants with serial MRI, and concurrently employ an evidence-based, tailored neuropromotive program before term age with the goal to optimize neurodevelopmental outcomes of VP infants. In this study, our aims are to investigate brain growth and development among VP infants receiving tailored neuropromotive support in the NICU compared to VP reference infants, and to characterize the timing and factors associated with total and regional brain growth and injury on serial brain MRI. Based on the results of initial imaging (initial brain MRI, or CUS if infant clinical status does not permit MRI imaging at the time of enrollment), infants will be assigned to either a low-risk or high-risk group, and subsequently receive protocolized, intensive in-NICU neuropromotive support tailored to their level of neurological risk until TEA. If subsequent imaging of an infant initially in the low-risk group indicates qualification for the high-risk group, the group assignment and the intensity of infant's neurodevelopmental support will be adjusted accordingly. The neuropromotive plan was designed based on an evidence-based program (28), adapted to include additional neurorehabilitative PT/OT support for high-risk infants with established neurological injury. We will explore the associations between risk-stratified NICU neuropromotive programming, and short-term (brain growth, neurobehavior, parent experience) and long-term (child development, family experience) outcomes of VP infants and their families.

The strengths of this study include the capability to obtain serial, in-unit MRI imaging, along with an expert-designed neuropromotive program that has been shown to impact clinical outcomes of VP infants in the NICU. Further, the program intensity will be amplified when higher grade neurological injury is identified, allowing for real-time intensive developmental therapy to facilitate neurorehabilitation. While some associations have been established between early interventions and neurodevelopmental outcomes, this study will contribute important mechanistic data which will broaden our understanding of how neuropromotive interventions can be best tailored for VP infants during a critical window of brain growth and development before TEA, for optimal downstream impact on child and family outcomes.

We acknowledge there are several limitations of this study. These include the prospective cohort study design which was chosen in order to achieve the primary aim of this study, i.e., to characterize brain growth and patterns of injury among VP infants. Infants in the current study are not randomized to SENSE intervention; rather, families of all eligible infants are approached for study consent. We recognize that infants whose families consent to the SENSE program (exposed) along with serial imaging may reasonably differ in their baseline characteristics from those who families do not initially consent to the SENSE program and serial imaging, but may subsequently agree to participate in the study as part of the unexposed, or reference group. We will address the potential for selection and confounding bias by evaluation of baseline demographic and clinical characteristics between group and adjusting statistical models as appropriate. Other limitations include the small size of the study with potentially limited power to detect a significant difference in effect between groups as well as the primary aim of this study being exploratory rather than hypothesis-driven; as such, observed associations between risk-stratified interventions and infant and/or family outcomes will be considered preliminary. Further, there may be imbalance in groups requiring oversampling in order to achieve at least 25 participants in each group.

## Ethics and dissemination

4.

The study protocol (#2019P003819) was approved through the IRB at Mass General

Brigham on 9/13/21. Dissemination of this work will occur through publication of short- (at NICU discharge) and long-term (2 years corrected age) infant and family outcomes in pediatric journals through a peer-review process. We anticipate that this work will contribute essential knowledge to further understand the relationships between brain development, brain plasticity, environmental experience, and outcomes in the vulnerable VP population. The results of this work may further inform optimal design of early neuropromotive interventions for hospitalized VP infants during a critical period of brain development prior to term age, with applicability in a large variety of NICU settings.

## Ethics statement

This study involving human subjects was approved by the Mass General Brigham Institutional Review Board. The study was conducted in accordance with the local legislation and institutional requirements. Written informed consent for participation in this study was provided by the participants' parents or legal guardians. Brigham and Women's Hospital Protocol Record 2019P003819, Serial Brain MRI in Hospitalized Preterm Infants, is registered in ClinicalTrials.gov Identifier: NCT06052865.
